## 6. Observations

### 6.1. Demographic Characterization—Baseline

Age;Country;Sex;BMI;Underlying neurological disease;Date of initial diagnosis;Charlson Comorbidity Index;Medication;ACSS score;Practice of sterile intermittent self-catheterization;Practice of clean intermittent self-catheterization;Duration of practised catheterisation in months;Number of catheterisations per day;Number of UTIs in last 12 months;Hospitalisation due to UTI;Earlier prophylaxis regimens/sufficiency of prophylaxis (prophylaxis regimen with duration and dosing, Patient impression, reduction of UTI in three months);Appropriateness of intermittent self-catheterization (measured by post-void residual (PVR) via ultrasound, which should be less than 100–150 mls).

### 6.2. Non-Antibiotic Prophylaxis Regimen

UroVaxom (OM-89) will be administered as a standard regimen: once daily for three months with a three-month pause following and three ten-day cycles at 7, 8 and 9 months.,StroVac (bacterial lysate vaccine) standard regimen: three vaccines in 6–12 weeks with two weeks between each vaccination *.Angocin twice daily for the duration of the study.D-mannose (oral dose 2 g) once daily for the duration of the studyBladder irrigation with saline (0.9%; 250 mL) once per day for the duration of the study.

* In case of restricted drug availability due to country-specific authorisation of vaccines, additional treatment arms with similar mechanisms of action will be opened and analysed as a subgroup. If necessary, amendments to the protocol will be issued, and additional ethics approval will be requested.

### 6.3. Evaluation at 3, 6, 9 and 12 Months (Table 1)

Number of UTI (reported by patient; if externally diagnosed and treated by, e.g., primary caregiver records will be obtained and added to study documentation);Hospital admission due to UTI or severe systemic infection (SOFA Score, SIRS criteria, Antibiotic administration, duration of hospital stays, urine culture);Antibiotic treatment/ treatment with a reserve antibiotic;Urine culture, including susceptibility profile;Rectal swab (optional);Perineal swab (optional);ACSS score;Adverse events during intake;HRQoL measures (subgroup of 30 patients);End at 12 months: patient impression (Likert Scale).

**Table 1 mps-06-00052-t001:** Summary of data collection points.

	Day 0	Month 3	6	9	12
*ACSS*	*X*	*X*	*X*	*X*	*X*
*Recruit*	*X*				
*Rectal swab*	*X ^*		*X ^*		*X ^*
*Perineal swab*	*X ^*		*X ^*		*X ^*
*CRF*	*X*	*X*	*X*	*X*	*X*
*Urine culture*	*X*		*X ^*		*X*

^ optional; ACSS = Acute Cystitis Symptom Score; CRF = Case Report Form.

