## Abstract

Introduction: Patients with neurogenic lower urinary tract dysfunction (NLUTD) reliant on intermittent self-catheterization for bladder emptying are at an increased risk of recurrent urinary tract infections (rUTI). So far, the most common practice in the prevention of rUTIs is long-term low-dose antibiotic prophylaxis, phytotherapy, and immunomodulation, whereby antibiotic prophylaxis inevitably leads to the emergence of drug-resistant pathogens and difficulty in treating infections. Therefore, non-antibiotic alternatives in the prevention of rUTIs are urgently required. We aim to identify the comparative clinical effectiveness of a non-antibiotic prophylaxis regimen in the prevention of recurrent urinary tract infections in patients with neurogenic bladder dysfunction who practice intermittent self-catheterization. Methods and analysis: In this multi-centre, prospective longitudinal multi-arm observational study, a total of 785 patients practising intermittent self-catheterisation due to NLUTD will be included. After inclusion, non-antibiotic prophylaxis regimens will be instilled with either UroVaxom^®^ (OM-89) standard regimen, StroVac^®^ (bacterial lysate vaccine) standard regimen, Angocin^®^, D-mannose (oral dose 2 g), bladder irrigation with saline (once per day). The management protocols will be pre-defined, but the selection of the protocol will be at the clinicians’ discretion. Patients will be followed for 12 months from the onset of the prophylaxis protocol. The primary outcome is to identify the incidence of breakthrough infections. The secondary outcomes are adverse events associated with the prophylaxis regimens and the severity of breakthrough infections. Other outcomes include the exploration of change in susceptibility pattern via the optional rectal and perineal swab, as well as health-related quality of life over time (HRQoL), which will be measured in a random subgroup of 30 patients. Ethics and dissemination: Ethical approval for this study has been granted by the ethical review board of the University Medical Centre Rostock (A 2021-0238 from 28 October 2021). The results will be published in a peer-reviewed journal and presented at relevant meetings. Study registration number: German Clinical Trials Register: Number DRKS00029142.

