We have recourse to a broad armamentarium of non-antibiotic options, whereby significant evidence is limited. Several viable and readily available options have been shown to yield consistent results. Main alternatives to antibiotic prophylaxis include vaccines, antiseptics, urine-specific antimicrobials, and direct mechanic washouts of the bladder. A variety of vaccines have been used in the prevention of rUTIs. Especially OM-89 (Urovaxom^®^) and the bacterial lysate vaccine Strovac^®^ have been diligently tested and proven to lower the rate of UTI [3,4,5,6]. Additionally, a wide variety of phytotherapeutics is currently in use, especially in Eastern medicine, as a cost-effective and low-threshold, whereas ambivalent efficacy has been reported. A combination of Tropaeoli majoris herba (Nasturtium) and Armoraciae rusticanae radix (Horseradish) demonstrated excellent safety and efficacy in the prevention of recurrent UTIs [7,8]. D-Mannose is another beneficial and cheap prophylactic, therapeutic agent in rUTI with very few side effects [9,10]. Bladder irrigation with various agents, e.g., neomycin, acetic acid, or sterile saline, is also widely used in order to lower bacterial load and defer sedimentation [11,12,13]. 

The main aim of our study is to identify the comparative clinical effectiveness of non-antibiotic prophylaxis regimens in the prevention of rUTI infections in patients with neurogenic bladder dysfunction who practise clean intermittent self-catheterization (CISC). The primary outcome is depicted by the number of breakthrough infections. Secondarily adverse events associated with the prophylaxis regimens and the severity of breakthrough infections must be investigated. 

Change in susceptibility pattern via the optional rectal and perineal swab, as well as health-related quality of life over time (HRQoL) outcomes, will be measured in a random subgroup of 60 patients.

The primary objective is to identify the clinical effectiveness of different prophylactic regimens. The secondary objective is to determine the adverse events related to prophylaxis and the severity of breakthrough infections. 

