## 2. Objectives

The aim of this prospective observational cohort study is to investigate the impact of five different non-antibiotic prophylaxis regimens over the course of one year on predefined time points. Our long-term goal is to identify safe and effective candidate regimens that could be carried to a randomised controlled trial (RCT) to establish clinical and cost-effectiveness. 

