### 2.2. Secondary Objectives

○Number of UTIs under non-antibiotic prophylaxis necessitating antibiotic treatment;○Evaluation of antibiotic resistance of inherent microbial flora and acquired urine cultures;○Evaluation of antibiotic consumption (DDD-defined daily doses) under non-antibiotic prophylaxis;○Evaluation of quality of life in patients undergoing non-antibiotic prophylaxis.

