## 3. Design

This is a prospective, longitudinal, multi-arm, multi-centre, observational, clinical cohort study. Patients will receive approved non-antibiotic UTI prophylaxis with either *Escherichia coli* viva OM-89 (UroVaxom^®^), bacterial lysate vaccine (StroVac^®^), nasturtium and horseradish root powder (Angocin^®^), D-Mannose or bladder irrigation with saline once daily. Occurring complications under named prophylaxis will be treated according to the current standard of care. 

Primary Outcome Measure: Incidence of symptomatic breakthrough infections.

Secondary Outcomes: Severity of infectious breakouts with antibiotic use, development of antibiotic-resistant (AMR) flora, number of antibiotics used, quality of life, and exploration of health economic assessment variables. 

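### The scheduled adverse event item is limited to an undefined intake period that differs by regimen, so safety data may not be comparable between arms that are all followed for 12 months

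*Protocol article*

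**What the plan says.** **Status of the outcome.** The Abstract states: "The secondary outcomes are adverse events associated with the prophylaxis regimens and the severity of breakthrough infections". Section 1.1 agrees: "The secondary objective is to determine the adverse events related to prophylaxis and the severity of breakthrough infections". Section 2.2 then lists four secondary objectives, beginning with "Number of UTIs under non-antibiotic prophylaxis necessitating antibiotic treatment" and going on to resistance, antibiotic consumption and quality of life. Section 3 gives "Severity of infectious breakouts with antibiotic use, development of antibiotic-resistant (AMR) flora, number of antibiotics used, quality of life", followed by health economic variables. Adverse events are in neither list.

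**Collection.** The item in Section 6.3, one list for all five regimens, is "Adverse events during intake". The UTI count in the same list carries no such limit. Section 6.4 lists adverse events among the items documented at stopping or dropout, and Section 7.3 says that events between data collection points will be investigated and reported. Neither section mentions intake.

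**Length of intake (Section 6.2).** Angocin, D-mannose and irrigation run throughout the study. UroVaxom is given "once daily for three months with a three-month pause following and three ten-day cycles at 7, 8 and 9 months". StroVac is three injections, with a course length of 6–12 weeks and a two-week gap between injections both stated. The Abstract sets follow-up at 12 months from the start of prophylaxis in every arm.

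**The concern.** The item ties the collection of adverse events to dosing, and dosing time differs widely by design. Taken at its word, a UroVaxom patient has nothing to report for the three-month pause, and a StroVac patient has nothing to report once the injections are over. A patient on a continuous regimen can report all year. UTIs are counted over the whole year in every arm, so benefit and harm would be observed over different periods within the same arm.

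This matters because the study compares regimens and Section 2 looks ahead to a trial: "Our long-term goal is to identify safe and effective candidate regimens". Section 7 describes categorical data by counts and percentages, with chi-square or Fisher tests. Percentages of patients with an event, taken over windows of unequal length, are not comparable. A later analysis plan could adjust for exposure time, but it cannot recover events that the form never asked for.

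**Working it through.** The article gives no adverse event rate and no window length, so there is no stated figure to reproduce. The check has two steps.

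**Step 1: window by regimen, reading intake literally.** Inputs are from Section 6.2; follow-up is 365 days.

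- Angocin, D-mannose, irrigation: 365 days (100%).
- UroVaxom: about 90 + 3 × 10 = 120 dosing days; 120/365 = 33%. Days outside intake: 365 − 120 = 245.
- StroVac, from first to last injection: 2 × 14 = 28 days using the two-week gaps (28/365 = 8%), or 42–84 days using 6–12 weeks (12–23%). The two statements do not give the same course length. Counting injection days alone gives 3/365 = 0.8%.

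The continuous window is 365/120 = 3.0 times the UroVaxom window, and 365/84 = 4.3 to 365/28 = 13 times the StroVac course. If intake is instead read loosely, as being assigned to the regimen, all windows are about 365 days and the ratio is 1.

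**Step 2: illustration of the effect on percentages.** Assume the same constant rate λ of events unrelated to treatment in every arm. The share of patients with at least one recorded event over d days is 1 − exp(−λ × d/365). The values of λ are assumptions.

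| Window (days) | λ = 0.25/year | λ = 0.5/year | λ = 1.0/year |
|---|---|---|---|
| Continuous regimens (365) | 22.1% | 39.3% | 63.2% |
| UroVaxom (120) | 7.9% | 15.2% | 28.0% |
| StroVac (84) | 5.6% | 10.9% | 20.6% |
| StroVac (28) | 1.9% | 3.8% | 7.4% |

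For example, at λ = 0.5: 1 − exp(−0.5) = 0.393 and 1 − exp(−0.5 × 120/365) = 0.152. The ratio of continuous to UroVaxom is 0.221/0.079 = 2.8 at λ = 0.25 and 0.632/0.280 = 2.3 at λ = 1.0. True rates are equal by construction, so the whole difference comes from the window.

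**The case against.** Four points can be made against this.

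1. *Adverse events are not recorded only during intake.* A reader might infer this from Section 6.3 alone, and the article does not support it: Sections 6.4 and 7.3 mention adverse events with no intake limit. This stands, but it does not close the gap. Section 6.4 reaches only patients who stop, and Section 7.3, under the heading of trial audit, sets no window and no method of collection.

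2. *Intake may be shorthand for being on the regimen.* The word fits neither an injection nor an irrigation, and Section 7 speaks of remaining on the same regimen, which cannot mean daily dosing for StroVac. This is a fair reading, and under it the windows are about equal. But the term is undefined, and centres could apply it differently.

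3. *The stated outcome is events related to prophylaxis, not background events.* This also stands. Fewer related events after a short course may be a true property of that regimen. So one cannot conclude that continuous regimens would look worse only because they are observed longer. What remains is that reactions appearing after the course or in the pause may not be captured, and relatedness can be judged only for events that are recorded.

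4. *An article leaves such detail to the full protocol and case report form.* That is often so. Here, however, the article does state a limit, and the limit is the problem.

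**Conclusion.** The point holds in a limited form. The scheduled item sets an undefined window that, read against Section 6.2, differs by regimen, and no other section sets a common one. Events in the UroVaxom pause or after the StroVac course may be missed, which would make adverse event percentages non-comparable between regimens.

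The size is uncertain. The ratio of windows runs from 1 on the loose reading to about 3 (UroVaxom) and 4–13 (StroVac course) on the literal one. The 39%, 15% and 4–11% figures rest on the literal reading and on an assumed equal, constant rate of unrelated events; they are not a forecast.

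A reader might go further and infer that the choice of safe candidates is biased. The article does not support that: it states a long-term goal, with no selection rule and no specified adverse event comparison.

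The absence of adverse events from Sections 2.2 and 3 is a real inconsistency with the Abstract and Section 1.1, but a minor one, since the events are collected in any case. It is separate from the window problem.

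**What to change.** - **Section 6.3:** replace the item with adverse events since the last visit, from first administration to month 12 in all regimens, whether or not the patient is currently taking the regimen. Add an on/off-treatment flag and the investigator's judgement of relatedness.
- **Reporting:** give events per patient-year by regimen. The flag keeps an on-treatment analysis available, and the relatedness judgement keeps the outcome as the Abstract words it.
- **Sections 2.2 and 3 (minor):** list adverse events as a secondary objective and outcome, to agree with the Abstract and Section 1.1.
- **Section 6.2:** reconcile the two statements of StroVac timing, so that the on-treatment period is defined.

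The cost is one reworded form item with two added fields, at visits that already take place, and one line in each of the two lists. The downside is that some more unrelated events will be recorded.

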### 6.4. Documentation of Stop Criteria/Study Dropout

Reason for dropout;Time Point of dropout;UTI;Sepsis;Adverse events;Problems of administration of the drug;Duration of non-antibiotic regimen;Switch to another prophylaxis regimen/which one.

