## 7. Statistical Considerations

Power analysis was performed to determine an adequate sample size. We considered that these patients suffer 9.4 UTIs per year with an SD of 5.414. Furthermore, we assumed that a reduction of 3 UTIs per year is clinically significant. In order to achieve an effect size of 0.1, 785 participants are necessary (power = 0.87; alpha = 0.05). Furthermore, to achieve an effect size of 0.2, 197 participants are necessary, or for an effect size of 0.3, 88 participants are required, respectively. Data measured on a continuous scale will be expressed as mean, standard deviation, range, and median. Counts and percentages of patients in the categories will be used to convey categorical data. When necessary, T- or Mann-Whitney tests will be performed to determine statistical differences in continuous variables, and Chi-square or Fisher’s tests will be used to test for statistical differences in categorical variables.

Patients with a minimum follow-up of 6 months who remained on the same prophylaxis regimen will be eligible for the final statistical analysis. 

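### Patient impression of the study regimen is collected only at month 12, with no rating at stop or switch, so this supporting measure will reflect mainly the patients who stayed

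*Protocol article*

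**What the plan says.** Section 6.3, headed "Evaluation at 3, 6, 9 and 12 Months (Table 1"), lists what is collected at the four follow-up evaluations. One entry is set apart for the last of them: "End at 12 months: patient impression (Likert Scale"). Table 1 has no separate row for it.

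Section 6.4 itemises what is documented when a patient stops or drops out. It begins "Reason for dropout;Time Point of dropout;UTI;Sepsis;Adverse events;Problems of administration of the drug", continues with how long the regimen was used, and ends with "Switch to another prophylaxis regimen/which one". None of these items is a rating by the patient.

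Section 7 defines who is analysed: "Patients with a minimum follow-up of 6 months who remained on the same prophylaxis regimen will be eligible for the final statistical analysis".

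Patient impression appears in one other place, the baseline list in Section 6.1, where it concerns regimens used before the study: "Earlier prophylaxis regimens/sufficiency of prophylaxis (prophylaxis regimen with duration and dosing, Patient impression, reduction of UTI in three months").

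**The concern.** A global impression is meant to show how acceptable patients found a regimen, and dissatisfaction is a plausible reason to stop or switch. If the question is put only at month 12, the patients most likely to give a poor score are also the most likely to be missing. Whether a rating is missing would then depend on the rating itself, which no analysis of the month-12 ratings alone can correct.

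Persistence may also differ by regimen. Section 6.2 sets a short vaccination course beside daily irrigation and daily or twice-daily oral products for the whole study. Ratings from those who stayed could therefore flatter some regimens more than others. Health-related quality of life is measured only in a subgroup (30 patients in the Abstract and Section 6.3, 60 in Section 1.1). That leaves the Likert item as the only overall patient rating of the study regimen planned for the whole cohort. At stake is the reading of this supporting measure, not the study's main results.

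**Working it through.** The plan states no figure on this point, so the check is first a reading of Sections 6.3, 6.4 and 7 together, then an illustration on assumed values.

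**Who ends up with a usable rating of the starting regimen**

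| Patient's course | In the Section 7 analysis set? | Rating of the starting regimen? |
|---|---|---|
| Stays on regimen and in follow-up to month 12 | Yes | Yes, at month 12 |
| Leaves follow-up before month 6 | No | None planned |
| Leaves follow-up between months 6 and 12, no switch | Yes | None planned |
| Switches regimen | No | None at the switch; a month-12 rating, if taken, falls outside the analysis |

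The baseline impression in Section 6.1 does not fill the gap, because it concerns earlier regimens.

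**How far the reported mean could be off**

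Let p be the share of starters without a usable rating, S the mean rating of those who stayed, and L the mean that the others would have given.

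- Mean over all starters = (1 − p) × S + p × L
- Reported mean = S
- Overstatement = S − [(1 − p) × S + p × L] = p × (S − L)

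The article gives none of p, S or L. Assumed ranges are p from 10% to 40% and S − L of 1 or 2 points:

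| p | S − L = 1 | S − L = 2 |
|---|---|---|
| 10% | 0.1 | 0.2 |
| 20% | 0.2 | 0.4 |
| 30% | 0.3 | 0.6 |
| 40% | 0.4 | 0.8 |

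**Comparison of two regimens**

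The difference between two regimens is distorted by the difference in their p × (S − L). Take 10% and 30% without a rating, a 2-point gap in both, and the same S. The reported means are equal, while the means over all starters differ by 0.3 × 2 − 0.1 × 2 = 0.4 points. If p × (S − L) is the same in both, the comparison is not distorted, although both scores are still too high. If those without a rating would have scored the same as those who stayed (S = L), there is no overstatement at all.

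**The case against.** The case against is substantial, and much of it stands.

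- **Impression is not a listed outcome.** It is absent from the outcomes in the Abstract, Section 1.1 and Section 3 and from the objectives in Section 2, and no comparison of it between regimens is planned. This stands and limits the point to a supporting measure. A reader might infer that the choice of candidate regimens for a later randomised trial is undermined. The documents do not support that: Section 2 ties the choice to safety and effectiveness, which rest on other data.
- **Dissatisfaction is recorded indirectly.** Section 6.4 captures reasons, timing, adverse events, administration problems and switches, so a large difference in dropout would be visible. This also stands, but these items are not on the Likert scale and cannot be set beside the month-12 score.
- **Leavers might still be rated.** A reader might infer that everyone who stops or switches goes unrated. The Abstract plans 12 months of follow-up, and nothing says that such patients skip the last evaluation. What remains is that no rating is planned at exit, and that a switcher's later rating would not enter the analysis.
- **Scores need not converge.** A reader might infer that all regimens drift to the same favourable score. Under Section 6.2 the StroVac course ends within 6 to 12 weeks, so a dissatisfied patient has little left to discontinue and can still rate poorly at month 12. Those who stay on a burdensome regimen may also rate it lower. Neither the direction nor the convergence is certain.
- **A single time point is coherent.** Pooling ratings from the moment of failure with month-12 ratings would change what is measured. This argues for separate reporting, not against collecting the exit rating.
- **The article is condensed.** Form content is often left to the case report form. Here, however, the article itself fixes the time of the rating and itemises the exit record.

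**Conclusion.** The point holds as a minor, inexpensive improvement. As written, the impression score for each regimen will reflect mainly patients who stayed on it and in follow-up, so it may be too favourable, by an amount that can differ between regimens. This follows from the rating time in Section 6.3, the absence of a rating in Section 6.4 and the exclusion of switchers in Section 7.

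The size cannot be derived from the document. The range of 0.1 to 0.8 points rests wholly on assumed shares of 10% to 40% and assumed gaps of 1 to 2 points. The 0.4-point example further assumes equal scores among those who stayed. The upward direction assumes that patients who leave or switch are on average less satisfied, which is plausible but not shown. The timing of this item does not affect the primary and secondary outcomes.

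**What to change.** Add the same Likert question to the Section 6.4 record, asked about the regimen being stopped, whenever a patient stops, switches or withdraws. Report by starting regimen, for all patients who started it:

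- the month-12 ratings and the number rated then;
- the exit ratings, with their time points and the number rated at exit;
- the number with no rating.

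State that the month-12 ratings alone are not to be read as the regimen's acceptability. Because early leavers and switchers fall outside the Section 7 analysis set, the report should say that this summary covers all starters.

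The cost is one question on a record that is already completed. Section 9.1 allows changes to the electronic case report form without a protocol amendment. The small downside is that exit ratings refer to different durations of use, so they should be shown separately and not pooled with the month-12 ratings as the main summary. The item should be added while patients are still being followed, since ratings missed at exit cannot be reliably recovered later.
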